#### Secondary objectives and endpoints

The secondary objectives and the corresponding endpoints are:

- Analysis of the impact of activity level and acquisition time on tracer accumulation assessed by visual and quantitative analysis. A 3D quantification will complete the semi-quantitative visual analysis. SPECT Volumetric Regions of Interest will be centered on 7 cartilaginous zones (three lumbar discs, two hips, two knees) then on the corresponding bony diaphyses or vertebral body or the adjacent muscles. The articular uptake of ^99m^Tc-NTP 15-5 will thus be normalized to bone or muscle uptake.- Analysis of pharmacokinetics (including excretion), biodistribution, and dosimetry of ^99m^Tc-NTP 15-5; the evolution of tracer activity/mL (AUC, Tmax and Cmax) will also be measured on whole blood and on plasma in the first 8 hours. Tracer urinary elimination over 8 h will be measured by counting.

Whole body planar (2D) and SPECT (3D) acquisitions will be performed for bio-distribution analysis and quantification of absorbed doses of tracer in target and non-target organs using a Monte-Carlo simulation and MIRD formalism (18). The analysis of ^99m^Tc-NTP 15-5 uptake intensity between osteoarthritis joints and normal joints will be carried out using visual methods and quantitative 3D analysis.

- The tolerance of ^99m^Tc-NTP 15-5 will be evaluated according to NCI-CTCAE (version 4.03). Tolerance assessments will include clinical examination, recording vital signs (heart rate, blood pressure, temperature, respiratory rate), weight, height, and OMS performance status; electrocardiogram (ECG); blood tests including full blood counts, prothrombin time, sodium, potassium, chloride, calcium, phosphorus, bicarbonate, serum total protein, serum albumin, fasting blood glucose levels, Thyroid-stimulating hormone (TSH), free thyroxine (fT4), free triiodothyronine (fT3), creatinine, urea, Alkaline phosphatase (ALP), Gamma-glutamyl transferase (GGT), Aspartate amino transferase (AST), Alanine amino transferase (ALT); 24-h urine collection tests: glucose, urea, creatinine, albumin, sodium, potassium, magnesium, calcium, and protein electrophoresis. Reporting of serious adverse events and suspected unexpected serious adverse reactions will be carried out according to the local regulations.

### Patients

#### Inclusion criteria

Inclusion criteria specific to group 1:

- Patients with painful unilateral osteoarthritis of the knee, such as femorotibial pattern defined by a radiographic score of 0/1 (Kellgren/Lawrence), and an average WOMAC score of 4 or more and by minor disorders on MRI (MOCART 2.0 score > 70).

Inclusion criteria specific to group 2:

- Patients with non-metastatic breast cancer, hormone receptor-positive, HER2-negative, with indication for adjuvant therapy with AI; treatment not yet started.- Age < 60 years.

Common inclusion criteria:

- Patients with at least 31 healthy joints (based on clinical assessment).- Signed written informed consent.- Affiliation to a health insurance plan.- For women of childbearing age (fertile, from menarche and to post-menopause unless sterile subsequent to surgery) including patients under GnRH agonist for ovarian suppression: negative serum pregnancy test at inclusion (fewer than 7 days before injection of ^99m^Tc-NTP 15-5). Menopause is defined as amenorrhea for at least 12 consecutive months without other cause and a level of FSH and estradiol consistent with levels of the post-menopausal period.- Willing and able to comply with study visits, treatment, examinations, and the protocol.

#### Non-inclusion criteria

- Patients < 18 years of age.- Pregnant or lactating patient.-BMI > 30.- History of known allergy to excipients present in the solution of ^99m^Tc-NTP 15-5.- Chronic inflammatory rheumatism (rheumatoid arthritis, spondyloarthropathy, psoriatic arthritis, etc.) diffuse arthritis (at least 3 joints affected), autoimmune connectivitis, fibromyalgia.- Known chronic joint pathology: osteoarthritis affecting at least 3 joints, autoimmune disease, inflammatory rheumatism (except unilateral knee arthritis).- Individuals deprived of their freedom, under guardianship/curatorship, or under legal protection measures.- Treatment with NSAIDs or cessation under 48 h previously.- Inability to comply with medical requirements/follow-up of the trial for geographic, family, social, or psychological reasons. These conditions should be discussed with the patient before registration in the study.

### Intervention

#### Study drug and administration

^99m^Tc-NTP 15-5 is synthesized by radioactive labeling with ^99m^Tc of the chemical precursor NTP 15-5, N-[(3-triethylammonio)propyl]- 1,4,7,10,13-pentaazacyclopentadecane, in presence of sodium pertechnetate (19). The synthesis of the pharmaceutical grade NTP 15-5 cold precursor is manufactured in accordance with GMP (Eras Laboratoire). The cold kit is manufactured in the experimental radiopharmacy unit in the Jean Perrin Center, in the form of a single-dose sterile kit.

The experimental drug is an injectable solution of ^99m^Tc-NTP 15-5with a molar activity greater than 2.5 GBq/μmol and radiochemical purity required to be over 90%.

According to the dose escalation plan, a single injection of 5, or 10, or 15 MBq/kg of ^99m^Tc-NTP 15-5 will be administered by slow intravenous injection on D0 in the presence of a nuclear medicine physician, without any premedication. Any treatment with NSAIDs will be discontinued at least 48 h before injection and can be resumed 24 h after injection. Prior and concomitant treatments will be collected at baseline and throughout the study.

#### Study procedures and participant timeline

Before any study-related assessment starts, written informed consent will be obtained from each patient. At screening/baseline (within 15 days before administration of ^99m^Tc-NTP 15-5), the patients will have a clinical evaluation noting vital signs, ECG, a specialized consultation with a rheumatologist, blood and urine tests, and a pregnancy test (for women of childbearing age), and for patients with osteoarthritis, an evaluation of osteoarthritis by MRI and X-ray dating from less than 2 months prior.

After checking the eligibility criteria, a dose allocation request will be performed using an eCRF.

The ^99m^Tc-NTP 15-5 dose at an activity level of 5, or 10, or 15 MBq/kg (according to the dose escalation plan), will be injected on D0 with a follow-up of vital signs: before, and 5 min, 10 min, 15 min, 30 min, 1 h, 2 h, 4 h, and 6–8 h after the end of infusion.

*e In vivo* biodistribution of ^99m^Tc-NTP 15-5 will be assessed using:

- Whole-body planar scintigraphy acquisition 30 min, 2 h, 4 h, and 6–8 h after injection on D0; SPECT acquisitions at 1 h, 2.5 h, 4.5 h, and 6–8 h after injection on D0; Computed Tomography will be carried out before the injection or at the time of SPECT acquisition.- Blood samples for the pharmacokinetic study will be collected at 5 min, 10 min, 15 min, 30 min, 1 h, 2 h, 4 h, and 6–8 h post injection on D0. An 8-h urine collection will be performed for excretion evaluation.

Patients will be followed for 1 week with a visit on D8 for safety evaluation with clinical examination, vital signs, blood and urine analyses, and ECG.

### Statistical considerations

A maximum of 6 patients should be included.

The number of subjects to be included takes into account the population selected and makes it possible to validate the hypothesis that healthy cartilage will present a significantly higher fixation than the adjacent diaphyseal fixation. For each patient, 31 observations (healthy joints) at 4 different times will be available for the evaluation of the main objective.

The optimal level of activity will be chosen using the dose escalation algorithm (Figure 1). The recommended dose will be defined as the dose from which 100% of patients present a score of 3 in at least 80% of healthy joints as observed on scintigraphy performed 2 h post-injection or less, and without DLT. If more than one time period (30 min or 2 h) meets these conditions, to choose the optimal time, we will perform a McNemar test where the number (minimum 2 patients, providing *n* ≥ 62 healthy joints) provides a power of 0.8, with an average effect size of 0.3 and an alpha risk of 0.05. For the moment, we do not have any element enabling estimation of the correlation with each patient.

Due to the nature and the design of the study, statistical analyses will be mainly descriptive. Missing data will not be replaced. The statistical significance threshold is set at 5%. Statistical analyses will be performed using R software.

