**Figure 1 F1:**
[figure not shown]
Dose escalation plan of CARSPECT study.

A maximum of 6 patients will be included in the study. A maximum of 4 patients will be included per dose level. The rule for termination will be that at least 2 patients have received the recommended dose level, with one patient from each group in the selected dose level. Recruitment will be carried out alternately in each of the 2 groups (breast cancer patients/osteoarthritis patients) as far as possible.

The recruitment period will be 24 months, with a follow-up period of 1 week, for a total duration of 25 months.

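### The McNemar test that picks between 30 min and 2 h counts joints from as few as two patients as independent, so its stated n, power and 5% level have no support

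*Protocol article*

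**What the plan says.** The Statistical considerations section of the protocol article sets a conditional rule for the case in which both 30 min and 2 h meet the criterion: "to choose the optimal time, we will perform a McNemar test where the number (minimum 2 patients". The size of that test is counted in joints: "minimum 2 patients, providing *n* ≥ 62 healthy joints". The section says this number "provides a power of 0.8", "with an average effect size of 0.3 and an alpha risk of 0.05". The next sentence reads "For the moment, we do not have any element enabling estimation of the correlation with each patient". It names no cluster-adjusted test, design effect or patient-level summary for this comparison, and it describes the analyses overall as mainly descriptive.

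Three other places matter:
- Study design (text at Figure 1) requires at least 2 patients at the recommended level and sets a ceiling: "A maximum of 4 patients will be included per dose level".
- Primary objective and endpoint already has the share of healthy joints at score 3 calculated for each patient.
- The same section and Statistical considerations require every patient to reach at least 80% of healthy joints at score 3, on an image taken no later than 2 h, without dose-limiting toxicity. The test is run only when both times pass.

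**The concern.** McNemar's test deals with the pairing of two times within one joint. It also assumes that the pairs are independent of one another. Here they are 31 joints inside each of 2 to 4 patients, and whatever makes one patient's contrast better at 30 min or at 2 h tends to move many of that patient's joints the same way. The independent units are the patients.

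Saying that the correlation is unknown does not remove the difficulty. Quoting 62, 0.8 and 0.05 with no allowance amounts to setting the correlation to zero.

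At stake is the choice of acquisition time, which the abstract's Discussion names with the dose as what the trial is to determine. The pooled test can report one or two patients' kinetics as a significant general effect of time. If it is not significant, the article gives no other way to choose.

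**Working it through.** **Inputs from the article:** 31 joints per patient; 2 patients at minimum and 4 at most per level; n ≥ 62; effect size 0.3 (scale not defined); alpha 0.05 (sidedness not stated); power 0.8; pass mark 80%, so 0.8 × 31 = 24.8, i.e. 25 joints. **Assumed, because the article does not give them:** the ICC, the spread of patient-level time effects, and the underlying share of joints at score 3.

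**1. The plan's own power figure, taking joints as independent.** Reading 0.3 as w in a 1-df chi-square test, the noncentrality is 62 × 0.3² = 5.58. Power is 0.66 two-sided and 0.76 one-sided; 0.80 would need 88 or 69 joints. At n = 62, two-sided, 0.80 is reached only with an unstated proportion of discordant joints: about 0.74 if 0.3 is a difference in proportions, 0.31 if it is Cohen's g, 0.40 if it is an odds ratio. The figure is therefore not reproducible from what is stated, which is less than saying it is wrong. A difference of 0.3 could not be observed when the test is run: both times have at least 25 of 31 joints at score 3, so they differ by at most 6/31 = 0.19.

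**2. Clustering.** Design effect = 1 + (31 − 1) × ICC of the time differences; effective n = 62 / design effect; power is two-sided at w = 0.3.

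| Assumed ICC | Design effect | Effective n | Power |
|---|---|---|---|
| 0 | 1.0 | 62 | 0.66 |
| 0.02 | 1.6 | 38.8 | 0.46 |
| 0.05 | 2.5 | 24.8 | 0.32 |
| 0.10 | 4.0 | 15.5 | 0.22 |
| 1 | 31 | 2.0 | 0.07 |

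The formula alone places the effective n anywhere from 2 to 62.

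**3. Error rate when the test is actually run.** Simulation of 2 patients × 31 joints with no average time effect. Each patient's time effect is normal with the SD shown, on the logit scale. Only runs in which both patients reach 25/31 at both times are kept. Entries are the rejection rate at nominal 5%, uncorrected / continuity-corrected (300,000 runs per setting before that selection).

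| Joints at score 3 | SD 0 | SD 1 | SD 2 |
|---|---|---|---|
| 85% | 1.2% / 0.5% | 3.2% / 1.7% | 4.2% / 2.4% |
| 90% | 3.0% / 1.4% | 7.9% / 4.9% | 11.6% / 7.6% |
| 95% | 4.6% / 1.1% | 10.8% / 4.8% | 19.2% / 11.5% |

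Four patients do not cure it: at 95% and SD 2 the rates are 19.0% / 13.5%.

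**4. Patient as the unit.** The smallest two-sided p of a sign or sign-flip test with k patients is 2/2^k: 0.50 for 2, 0.25 for 3, 0.125 for 4. None reaches 5% at one dose level.

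**The case against.** The best defence is that the test is only a tie-breaker. It runs after both times have qualified in every patient, it touches neither the dose nor the toxicity rule, and a wrong pick is still a qualifying time. The article discloses that the correlation is unknown, calls its analyses mainly descriptive, and already computes per-patient ratios. All of that stands, and it limits the severity.

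The pass mark also limits the size. A reader might put ICCs of 0.02, 0.10 and 0.30 into 2 × (1 − Φ(1.96/√design effect)) and infer error rates of 12%, 33% and 54%. Those figures ignore the condition for running the test. With at most 6 joints per patient able to move one way, and no average time effect, the ICC among tested trials cannot exceed about 0.17 to 0.19. At 0.17 the design effect is 1 + 30 × 0.17 = 6.1 and the effective n about 10, so an effective n of two is also excluded. At 85% of joints at score 3, the simulated error stays below 5%.

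Three further inferences are not supported:
- **That no valid patient-level test could reach 5%.** This is true of sign and sign-flip tests, but a paired t-test on patient proportions can reach it if normality is accepted.
- **That "31 observations (healthy joints) at 4 different times will be available for the evaluation of the main objective" is an error.** Study procedures schedules four planar acquisitions, and the criterion itself is limited to 2 h or less.
- **That the chosen time passes straight into phase II.** The Discussion ties phase II to the validated activity only.

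The lack of a rule for a non-significant result may be covered in the full protocol, so it is not counted as a separate fault.

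The defence does not supply a basis for 62 independent observations or for power 0.8. The article itself fixes the method, n, power and alpha, so this is not detail left to another document.

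**Conclusion.** The point holds, at moderate severity. The joint-based n ≥ 62, the power of 0.8 and the 5% level assume an independence that the article says it cannot assess, with only 2 to 4 patients behind the test. Among trials where the test would be used, the error is about 8 to 19% uncorrected and about 5 to 11.5% continuity-corrected, for 2 patients, time effects of SD 1 to 2 logits and 90 to 95% of joints at score 3. These ranges rest on assumed inputs, and the article does not say which version of the test is meant. With smaller patient-level effects or fewer joints at score 3, the inflation may vanish. The stated n and power would still lack support. A reader might infer that the recommended dose is compromised; it is not, because this test plays no part in setting it.

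**What to change.** In Statistical considerations:

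1. Remove the joint-pooled McNemar test as the rule for choosing the time, and withdraw the n ≥ 62 and power 0.8 statement.
2. Report each patient's proportion of score-3 joints at 30 min and at 2 h, using the ratio already defined under Primary objective and endpoint.
3. Pre-specify a descriptive choice: the time with the higher mean per-patient proportion, with a tie broken by the higher minimum. This also yields a choice where the test would have been non-significant.
4. If a McNemar result is still shown, label it exploratory and state that 2 to 4 patients are too few for a reliable cluster adjustment.

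The statement about four acquisition times needs no change. The cost is a few sentences and the loss of a p-value. No additional patients, images or readings are needed, and the change fits the article's own description of its analyses as mainly descriptive.

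### The stated McNemar power of 0.8 for 62 joints cannot be reproduced from the effect size and alpha printed with it

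*Protocol article*

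**What the plan says.** The Statistical considerations section of the protocol article sets out a contingent test: "If more than one time period (30 min or 2 h) meets these conditions, to choose the optimal time, we will perform a McNemar test". The conditions are those for the recommended dose: every patient has score 3 in at least 80% of healthy joints on a scan at 2 h or earlier, with no DLT.

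The size of the comparison is given as "minimum 2 patients, providing *n* ≥ 62 healthy joints", which is 2 × 31. The same section confirms the multiplier: "For each patient, 31 observations (healthy joints) at 4 different times will be available". It then states that this number "provides a power of 0.8, with an average effect size of 0.3 and an alpha risk of 0.05".

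The section does not say what kind of effect size 0.3 is, whether the test is one- or two-sided, or what proportion of joints is expected to be discordant between the two times. It adds that nothing is available to estimate the correlation within a patient, and that the analyses will be mainly descriptive.

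**The concern.** This is the only power statement in the article, and it prints n, effect size, alpha and power together, so it can be checked. If the four figures do not fit, the article promises more from the 2-patient minimum than that minimum delivers.

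This is separate from clustering. No allowance for within-patient correlation is made, so the stated figure already treats the 62 joints as independent, which is the favourable case. What is at stake is how a reader weighs the test that picks the acquisition time, one of the methodological choices the article's abstract says the trial should settle.

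**Working it through.** **Inputs from Statistical considerations:** n = 62 joints (2 × 31), effect size 0.3, alpha 0.05, stated power 0.80. **Assumptions made here:** independent joints, and two-sided testing unless noted.

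**1. Attempt to reproduce 0.80, reading 0.3 as a medium standardised effect.** This reading needs no further input.
- Chi-square on 1 df, noncentrality n·w² = 62 × 0.09 = 5.58: power 0.656.
- n for 0.80: (1.960 + 0.842)² / 0.09 = 7.849 / 0.09 = 87.2, so 88 joints.
- Effect giving 0.80 at n = 62: (1.960 + 0.842) / √62 = 0.356.
- One-sided: Φ(0.3·√62 − 1.645) = Φ(0.717) = 0.763.
- Paired t approximation, d = 0.3: 0.642 two-sided, 0.755 one-sided.
- McNemar normal approximation with (p10 − p01)/√ψ = 0.3, where p10 and p01 are the two discordant proportions and ψ is their sum: Φ((0.3·√62 − 1.960)/√(1 − 0.09)) = 0.663.

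None of these gives 0.80.

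**2. The McNemar test itself, by enumeration.** The approximation in the last line does not depend on ψ, but the test does. Standardised effect 0.3, n = 62:

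| Discordance ψ | Uncorrected test | Exact test |
|---|---|---|
| 0.09 (all one direction) | 0.82 | 0.49 |
| 0.12 | 0.75 | 0.56 |
| 0.15 | 0.71 | 0.58 |
| 0.20 | 0.69 | 0.59 |
| 0.25 | 0.69 | 0.60 |
| 0.387 | 0.69 | 0.60 |

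The uncorrected test reaches 0.80 only near 9% discordance with every discordant joint favouring the same time. The exact test does not reach it.

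**3. Reading 0.3 as a raw difference in proportions.** Power = Φ((0.3·√62 − 1.960·√ψ)/√(ψ − 0.09)). This gives 0.88 at ψ = 0.60, 0.80 at ψ = 0.739 and 0.71 at ψ = 0.90. So 0.80 requires an unstated discordance of about 74%.

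The condition for running the test does not allow that. Score 3 in at least 80% of 31 joints means at least 24.8, so 25 joints, leaving at most 6 below score 3 per patient at each time. Over 2 patients:
- maximum observed difference: 12/62 = 0.19;
- maximum observed discordance: 24/62 = 0.39.

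Both limits lie well below 0.30 and 0.74.

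**4. Reading 0.3 as Cohen's g (an 80:20 split of discordant joints).** Power of 0.80 needs about 20 discordant joints. At that split the same condition allows at most 12 + 3 = 15, where power is 0.65.

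**The case against.** The strongest reply is that the article never names the metric. McNemar power cannot be computed without the discordant proportions or an equivalent, and the full protocol, which is not shown, may define them. This stands in part. It means that 0.66 belongs to one reading, and a reader who took it as the trial's true power would go too far. It does not rescue 0.80: the standardised reading falls short outside one corner case, and the raw-difference and Cohen's g readings need more discordance than the plan's own condition permits.

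The figures in steps 1 and 2 also do not condition on the test being triggered. If they did (simulation of 2 × 31 independent joints, standardised effect 0.3, no joint below score 3 at both times, uncorrected test), power would be about 0.81 at 9% discordance, 0.64 at 15%, 0.51 at 20% and 0.37 at 25%. This is a further reason not to present 0.66 as a property of the test as it would be run.

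The 62 joints are a floor. On the w = 0.3 reading, 3 patients (93 joints) would give about 0.82, and the article allows up to 4 patients per dose level. But the sentence attaches 0.8 to the 2-patient minimum.

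A reader might infer that a non-significant result will be taken to show that the two times are equivalent. The article plans no such conclusion. A reader might also infer that the recommended dose or the enrolment is undermined. Neither follows: the dose comes from the 100%-of-patients, 80%-of-joints and no-DLT rule, and the 2-patient minimum is also the termination rule in Study design, with one patient from each group.

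**Conclusion.** The concern holds in limited form: the stated power of 0.8 cannot be reproduced from the figures beside it. With w = 0.3, 1 df, two-sided alpha 0.05 and independent joints, power is about 0.66, which is 14 points lower. On that reading 0.8 would need about 88 joints or an effect of about 0.36.

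Confidence is high that 0.8 does not follow in general. It is lower for any single replacement value, because the metric, the discordance and the version of the test are not given. Positive within-patient correlation that reduced the effective number of joints would lower power further. The consequence is confined to the choice between two acquisition times that have both already qualified.

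**What to change.** Either of two changes to one sentence in Statistical considerations would do:

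- **Delete the power claim** and call the 30 min versus 2 h comparison descriptive, in line with what the section says about its analyses generally. This is the simpler choice.
- **Define and restate.** Give the effect size as the two discordant proportions, name the version of the test and its sidedness, and restate the power for 62 joints under independence. If w = 0.3 was intended, that is about 0.66, labelled as an approximation for that reading, with 0.8 reached at an effect of about 0.36. The proportions chosen should be compatible with the 80% condition at both times.

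The cost is one sentence and a less favourable stated power. No patients, scans or procedures are added, and the dose rule is untouched.
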